### Procedure

#### Study Visits and Follow-Up Calls

A schematic diagram summary of the time-schedule of visits, rewards, and data collection at each visit is shown in Multimedia Appendix 1.

#### Enrolment Visit

During the enrolment visit (visit 1) participants are asked to complete a battery of questionnaires and provide 2 CO breath samples. Regardless of group allocation, participants are asked to nominate a support person (they are asked to have this person in mind when completing the Partner Interaction Questionnaire), preferably the person they are living with (eg, partner or family member), whose contact details are recorded along with the participant’s own details to assist with future correspondence. While no smoking cessation counseling is provided, participants are offered a resource pack for themselves and their support partner.

#### End-of-Pregnancy Visit

Regardless of smoking status, all participants are required to attend an end-of-pregnancy study visit. This second visit occurs at approximately 8 months gestation and participants are asked to provide 2 CO samples and complete a series of questionnaires.

#### End-of-Study Visit

Regardless of smoking status, all participants are required to attend an end-of-study visit, which occurs at approximately 2 months postpartum. Participants are asked to provide 2 CO samples and complete a series of questionnaires including the End-of-Study Questionnaire.

#### Monthly Telephone Calls and Verification Visits

Monthly telephone calls are conducted with all participants to determine smoking status. During the phone calls, participants are asked “Have you had a cigarette (even a puff) in the past 7 days?” If a participant self-reports as abstinent, they are invited to attend a follow-up verification visit to verify their smoking status (and receive a voucher incentive), which is booked at their next convenience. If the participant self-reports smoking in the last 7 days during the monthly telephone call, they are advised that they are not eligible for the incentive that month and will be contacted again the following month. This monthly payment schedule limits the additional participation burden on participants, and where possible, is scheduled on days when they are attending routine hospital antenatal appointments. This monthly payment schedule was also utilized by the only other study published using incentivized partner support [23]. Participants who verify as abstinent at their end-of-study visit (visit 3) are eligible to receive monthly calls and incentives until 6 months postpartum. Participants who are still smoking at the end-of-study visit no longer receive monthly calls (and are ineligible for any further incentives) from that date. Multiple (up to 5) attempts are made to contact each participant for their scheduled monthly telephone calls and visits. Text messages (short message service, SMS) are also utilized to try to contact those difficult to reach. However, the study adopts an intention-to-treat approach such that if participants become un-contactable at any time throughout the study, it is presumed they are smoking [28].

#### 12-Month Telephone Call and Visit

Each participant, regardless of smoking status, is contacted via telephone 12 months after the delivery of their baby. The 12-Month Follow-Up Questionnaire is administered via telephone and participants are asked their current smoking status. Participants who self-report abstinence (7-day point prevalence) during this call are invited to verify smoking abstinence via a CO breath sample in a follow-up visit and be offered an AUD$10 shopping voucher (regardless of verification status) to thank them for their participation. This marks the completion of their participation in the study.

### Study Questionnaires

A battery of questionnaires are issued to participants during study visits.

#### Baseline Questionnaire

The Baseline Questionnaire was developed to obtain demographic information (eg, age, highest level of education, income), information about smoking characteristics (eg, smoking status, cigarettes per day, dependence [Fägerstrom Test for Cigarette Dependence [29]], smoking history, and partner’s smoking characteristics), and pregnancy (eg, gestation, gravidity, smoking during previous pregnancies). This questionnaire is administered only once at study enrolment (visit 1).

#### Smoking Knowledge Quiz

The Smoking Knowledge Quiz was developed from existing publicly available and scientifically reliable smoking information and is similar to the questionnaire used in a previous study [30]. The quiz requires participants to answer questions regarding their knowledge of the safety and effectiveness of smoking cessation treatments and techniques during pregnancy, as well as the health risks associated with cigarette smoking for themselves and their baby. Participants’ responses to this quiz are reviewed with the participant at the time of the enrolment visit to prompt discussion of health risks and available cessation aids. The quiz is administered once only at study enrolment (visit 1).

#### Smoking Status Questionnaire

The Smoking Status Questionnaire is a self-report, 14-day cigarette timeline follow-back which requires participants to report the number of cigarettes smoked each day for the previous 2-week period [31]. This questionnaire is completed at each study visit.

#### Reasons for Quitting Questionnaire

The Reasons for Quitting Questionnaire (RFQ) is a 24-item questionnaire measuring an individual’s motivation for quitting [32]. Reponses to items such as “I want to quit smoking because I am concerned that I will suffer from a serious illness if I don't quit” are scored on a 5-point Likert scale from 0 (not at all true), to 4 (extremely true). This questionnaire is completed at each study visit.

#### Partner Interaction Questionnaire

The Partner Interaction Questionnaire (PIQ) is used to gather information about the level of partner support [33]. It includes 10 positive (PIQ-POS) (eg, “Express pleasure at your efforts to quit”) and 10 negative (PIQ-NEG) (eg, “Comment on your lack of willpower”) partner behaviors that could be expressed towards a quitting partner. This questionnaire is completed at each study visit.

#### End-Of-Study Questionnaire

The End-of-Study Questionnaire was developed to collect information after participants have had their baby and is conducted around 2 months postpartum during the scheduled end-of-study visit (visit 3). This questionnaire includes questions about smoking status, cigarettes per day, experience of study participation and receiving incentives, treatments/methods used to aid quit attempt, partner support, and partner smoking status, as well as any birth complications experienced.

#### 12-Month Follow-Up Questionnaire

The 12-Month Follow-Up Questionnaire is administered via telephone during the 12-month follow-up telephone interview. This marks the completion of study participation. Participants are asked to describe their smoking status, experience of being in the study, details of partner support of quit attempts, and their overall general well-being and that of their baby. If participants are quit, they are invited to return to the study center to verify.

Fetal growth and birth outcomes are also collected from babies of consenting participants (a separate consent form is provided seeking access to this information) including head circumference, femur length, heart/vascular data, birth weight, Apgar score (overall health at birth), gestational age, and digital medical records of neonatal intensive care unit (NICU) or respiratory admissions (if applicable). These data will be used for exploratory analyses to determine any associations with intervention effects.

### Sample Size and Checks

The study is powered on the primary hypothesis (H1) which requires a sample size of 108 (see below). This is consistent with a review of previous research in the area, which revealed sample sizes ranging between 40 and 220 with approximately equal group sizes [17]. To ensure particular features of the study protocol do not influence the data, checks will be conducted during the analysis phase to control for influence of different antenatal service sites being used for recruitment and testing, as well as any cyclical effects of the cyclical monthly recruitment design.

### Planned Analyses

Analyses are planned to test each of the 4 hypotheses.

#### Hypothesis 1

The first hypothesis (H1) is that providing an incentive to both the support partner and expectant smoking mother to quit is more effective than providing an incentive to the pregnant smoker alone at promoting abstinence during pregnancy.

The quit rates of the treatment and control groups will be compared at the end-of-pregnancy time point (visit 2) using chi-square analysis. While no study to our knowledge has compared participant-only incentive with combined participant and support partner incentive, Donatelle et al [23] compared a usual care control group with an incentive plus partner incentive treatment group and found that at the end-of-pregnancy, 32% of treatment group participants had quit (n=105) compared with 9% in the control group (n=102), which indicates a large effect size (*χ*^2^=18.4, N=207, *d*=0.62) [23]. Since the control group in the present study is also receiving incentives, it is anticipated that the effect size may be moderate, rather than large. As such, to determine if there is a significant difference in proportion of women who have quit between control group and treatment group, with the power of .80 to detect an effect size of 0.30, the study will require a total sample size of 108.

#### Hypothesis 2

The second hypothesis (H2) is providing an incentive to both the support partner and expectant smoking mother to quit is more effective than providing an incentive to the pregnant smoker alone at promoting abstinence in the postpartum period.

As per H1 above, treatment and control group abstinence rates will also be compared at the end-of-study (visit 3) and at 12-months postpartum follow-up time points to determine the effect of incentivized partner support on postpartum abstinence. A multi-comparison adjustment will be applied to control for family-wise error.

#### Hypothesis 3

The third hypothesis (H3) is regardless of incentives, women who receive more positive cessation support from their partners (as measured by PIQ-20) are more likely to quit smoking.

Participants, regardless of group allocation, will be regrouped to either PIQ-POS or PIQ-NEG, as determined by the ratio of positive compared to negative support they report receiving from their support partners. The abstinence rates of these regrouped PIQ-POS and PIQ-NEG participants will then be compared at 3 time points; end-of-pregnancy, end-of-study (2 months postpartum), and 12 months postpartum.

#### Hypothesis 4

The fourth hypothesis (H4) is providing incentives for pregnant smokers to quit is more effective than “usual care” antenatal smoking cessation support at promoting smoking cessation.

The quit rates of participating women will be compared to the average quit rate of a historical control of women receiving antenatal care by the Tasmanian Health Service from 2011 to 2015 [34].

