## Methods

### Trial Design

This study will adopt a non-randomized, single-blinded, controlled 2-group (control and treatment) trial design.

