### Assignment of Interventions

Participants are assigned to the same group (either control or the treatment group) for 3 consecutive months (interchangeably for 18 months), such that participants recruited in the first 3 months are allocated to the control group and participants recruited in the following 3 months are allocated to the treatment group. This design was chosen to assist participant blinding to group allocation, given the heightened potential for the women recruited to know each other and/or discuss research participation. Since participants in this study are recruited following their first antenatal appointment, participants recruited around the same time will have similar due dates. As membership to parents’ groups and hospital-run parentcraft classes is usually assigned by due date/gestation, and due to the relatively small recruitment pool (Tasmania has a population of 515,000 and only 3 tertiary hospitals), adopting a fully randomized, parallel group controlled design would likely jeopardize participant allocation concealment (ie, differing incentive amounts), thus introducing bias (eg, recruited women declining/delaying enrolment due to allocation, participants not being as motivated to quit smoking due to lesser incentive amount). As well as assigning participants to the same group in 3-month intervals, participants who report knowing another participants or are recruited by another participant are assigned to the same group.

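### The primary H1 test, and H2 with it, is an unadjusted chi-square although arm is set by recruitment block and acquaintance, so measured baseline differences between the women stay in the estimated effect

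*Protocol article*

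**What the plan says.** Under Trial Design: "This study will adopt a non-randomized, single-blinded, controlled 2-group (control and treatment) trial design". Under Assignment of Interventions: "Participants are assigned to the same group (either control or the treatment group) for 3 consecutive months (interchangeably for 18 months", control first. That section also has an exception to the calendar rule: "participants who report knowing another participants or are recruited by another participant are assigned to the same group".

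Under Planned Analyses, Hypothesis 1: "The quit rates of the treatment and control groups will be compared at the end-of-pregnancy time point (visit 2) using chi-square analysis". Hypothesis 2 follows H1: "treatment and control group abstinence rates will also be compared at the end-of-study (visit 3) and at 12-months postpartum follow-up time points", with a family-wise error adjustment. No covariate, stratum or regression model is named for either hypothesis.

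The Baseline Questionnaire, given once at visit 1, records "demographic information (eg, age, highest level of education, income" and "information about smoking characteristics (eg, smoking status, cigarettes per day, dependence", as well as smoking history, the partner's smoking and gestation. The Enrolment Visit section adds two CO samples. None of these enters the stated H1 or H2 analysis.

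Sample Size and Checks promises checks at the analysis phase to "control for influence of different antenatal service sites being used for recruitment and testing" and to deal with cyclical recruitment effects. It gives no method.

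**The concern.** A crude comparison of quit rates can be read as the effect of incentivising the partner only if the women in the two arms are otherwise comparable. Randomisation would make them so on average, but here the calendar and social ties decide the arm. The Participant Recruitment section describes several entry routes: calls by a research midwife, staff referral, flyers, self-referral and possible media exposure. The mix of women entering can therefore differ from one 3-month block to the next. The acquaintance rule also places socially linked women in the same arm.

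At stake is the study's main causal claim. If one arm happens to enrol less dependent smokers, or fewer women with smoking partners, the chi-square reports that difference as a treatment effect. A SAP could add detail, but this document has already named the unadjusted test for the primary hypothesis, while the variables needed for something better are being collected.

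**Working it through.** The plan gives no figure for baseline imbalance or for an adjusted effect, so there is none to reproduce on this point. Its total of 108 is used only to set 54 women per arm.

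**1. What the checks can reach.** Eighteen months in 3-month blocks gives six blocks: control in 1, 3 and 5, treatment in 2, 4 and 6. Blocks 1 and 5 fall in the same calendar quarter and are both control. Blocks 2 and 6 share another quarter and are both treatment. Blocks 3 and 4 stand alone in the other two quarters. Every quarter therefore lies in one arm only, acquaintance exceptions aside, and a check using quarter as a factor cannot separate season from arm. A site check is feasible, but it does not concern differences between women.

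**2. Size of the bias (illustration; all inputs assumed).** Take a binary baseline predictor, no treatment effect, and average prevalence 50%. Let the quit-rate gap between its levels be *g*, and the difference in its prevalence between arms be *δ*. Then

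- control quit rate = *q*_low + *g*(0.5 − *δ*/2)
- treatment quit rate = *q*_low + *g*(0.5 + *δ*/2)
- spurious difference = *g* × *δ*

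Rejection rates come from 20,000 simulated trials per row, 54 women per arm, two-sided 5% level. The comparator is a Cochran-Mantel-Haenszel test stratified on the predictor.

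| Quit rate by predictor | *δ* | Control / treatment | *g* × *δ* | Chi-square type I error | Stratified type I error |
|---|---|---|---|---|---|
| 35% v 15% | 10 points | 24% / 26% | 0.20 × 0.10 = 2 points | 5.2% | 4.5% |
| 35% v 15% | 20 points | 23% / 27% | 0.20 × 0.20 = 4 points | 7.5% | 5.1% |
| 40% v 10% | 10 points | 23.5% / 26.5% | 0.30 × 0.10 = 3 points | 6.1% | 4.9% |
| 40% v 10% | 20 points | 22% / 28% | 0.30 × 0.20 = 6 points | 10.5% | 4.9% |

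With *δ* = 0 the chi-square rejects in 5.0% and 5.2% of runs, so the excess comes from the imbalance and not from the test.

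**3. Scale against the planned effect.** Read the stated effect size of 0.30 as Cohen's *w*, that is (p1 − p0) / (2√(p̄(1 − p̄))) = 0.30. A control quit rate of 9% then implies 33.6% on treatment, a difference of 24.6 points. A control rate of 32% implies 61.9%, a difference of 29.9 points. The illustrated bias is thus between 2/29.9 = 7% and 6/24.6 = 24% of the difference the study is sized to detect.

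**The case against.** The plan does not ignore its design. It names site and recruitment cycle as threats and says it will control for them, so a reader who infers that nothing at all is adjusted goes too far. Alternating blocks limit confounding by a slow time trend. Participant blinding is meant to stop women declining or delaying enrolment because of the arm, and the research midwife's calls are directed at all women who report smoking at booking. The article is condensed, and the method of a check is the kind of detail that a SAP supplies. All of this stands. It narrows the point, because the checks as described do not reach woman-level differences and are not part of the stated H1 test.

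Four stronger readings are tempting and unsupported:

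- That enrolling staff knew the arm and could select women. This is a natural inference from a single-blinded design with a calendar schedule, but no section states it.
- That the baseline variables are strong predictors of quitting. The document does not say so; it is a subject-matter assumption.
- That large chance imbalances show bias. With 54 per arm, a covariate of 50% prevalence differs between randomised arms with SD √(2 × 0.25/54) = 9.6 points, but a chi-square under randomisation already allows for that. Only systematic differences between blocks matter here.
- That the chi-square is invalid as a test. It remains a test of association; what fails is the step to a causal reading. An adjusted model also needs the assumption of no unmeasured confounding.

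**Conclusion.** The point holds in limited form. The document fixes an unadjusted primary test for a comparison that is not randomised, carries it to H2, and leaves unused the baseline variables that could remove measured confounding. The size is illustrative only: 2 to 6 points, with type I error close to nominal (5.2% to 6.1%) at a 10-point imbalance and raised (7.5% to 10.5%) at 20 points. These figures rest on an assumed predictor, assumed quit rates and assumed imbalances.

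A reader might infer that the trial's result will be biased in favour of the partner incentive. The documents do not support that: they give no baseline data by arm, so neither the direction nor the presence of an imbalance is known. The case for change is that the better method is cheap and uses data already being collected.

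**What to change.** Before outcomes are compared, pre-specify a covariate-adjusted analysis as the main estimate for H1, and the same model for H2:

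- Logistic regression of quit status on arm with a short fixed list, for example dependence score, gestation at enrolment, partner smoking and site. Use only one smoking-intensity measure, since dependence, cigarettes per day and CO are likely to overlap.
- Firth penalisation if quitters are few.
- Report a standardised risk difference with 95% CI.
- Keep the chi-square as the supportive unadjusted result.
- Show baseline characteristics by arm and by recruitment block.
- State how the site and cycle checks will be done, and that unmeasured and seasonal differences between blocks cannot be removed.

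The cost is analysis wording and one model, with no new data. Events limit the list. Assuming 25 to 35 quitters in total, arm, three single-term covariates and two terms for the three sites make 6 parameters, or 25/6 = 4.2 to 35/6 = 5.8 events per parameter. A fourth covariate lowers this to 25/7 = 3.6 to 35/7 = 5.0. The reason to adjust is bias. A precision gain should not be promised, because adjustment in logistic regression does not generally shrink the standard error of the log odds ratio. Residual confounding remains. Fixing the list now also prevents the adjusted result from looking selected after the fact.

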### Objectives

The purpose of this study is to determine whether providing incentives to both support person and expectant mother, if she is able to quit smoking, is more effective than providing incentives to expectant mother only, in promoting short- and long-term smoking cessation during pregnancy. In essence, the present study seeks to answer the question: “Can partners (eg, spouse) be incentivized to be more supportive and effective quit buddies to their pregnant smoking partners?”

Specifically, the study aims to determine whether (1) providing an incentive to both the support partner and expectant smoking mother to quit is more effective than providing an incentive to the pregnant smoker alone at promoting abstinence; (2) regardless of incentives, women who receive more positive cessation support from their partners, as measured by the Partner Interactive Questionnaire 20 (PIQ-20), are more likely to quit smoking; and (3) providing incentives for pregnant smokers to quit is more effective than “usual care” antenatal quit smoking services such as brief advice and referral to smoking cessation services (external telephone counseling and smoking cessation nurse) at promoting smoking cessation.

The primary outcome for the study is smoking status (ie, smoking or quit), as determined by self-report 7-day point prevalence, and carbon monoxide (CO) less than 7 particles per million (ppm) at the end-of-pregnancy time point. Secondary outcomes include effect of incentives on long-term (2 months and 12 months postpartum) abstinence and influence of the quality of partner support (positive compared to negative supportive behaviors) on smoking status.

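### The planning effect of 0.30 is not smaller than the earlier study's effect: on the chi-square scale it is the same effect, and on the d scale 108 women give about 34% power

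*Protocol article*

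**What the plan says.** The Trial Design section describes a "controlled 2-group (control and treatment) trial design", and the Objectives section makes the outcome binary: "The primary outcome for the study is smoking status (ie, smoking or quit" and so on. Under Planned Analyses, Hypothesis 1, the primary test is fixed: "The quit rates of the treatment and control groups will be compared at the end-of-pregnancy time point (visit 2) using chi-square analysis".

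The same paragraph takes its effect size from an earlier trial of incentives for woman and supporter against usual care: 32% of 105 against 9% of 102 had quit, reported as chi-square 18.4, N=207, d=0.62, and labelled large. Because both groups here receive incentives, "it is anticipated that the effect size may be moderate, rather than large". From this it concludes "with the power of .80 to detect an effect size of 0.30, the study will require a total sample size of 108".

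Sample Size and Checks relies on that figure: "The study is powered on the primary hypothesis (H1) which requires a sample size of 108". The article gives no metric for 0.30, and no alpha, degrees of freedom, assumed quit rates or dropout allowance. The only effect-size metric it names is d, in the preceding sentence.

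**The concern.** The argument runs from a large effect to a smaller one, and the printed numbers fall from 0.62 to 0.30, so the reader sees an effect roughly halved. That holds only if both numbers are on the same scale. If 0.62 is d and 0.30 is w, the drop may come only from the change of scale, and the trial would be sized for the effect that the authors say they do not expect. If 0.30 is also d, the sample size is far too small for the stated power.

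At stake is the reading of the primary result. The trial looks for what partner incentives add to incentives for the woman alone. If it is described as having 80% power for a moderate effect but has that power only for one close to the earlier usual-care contrast, a non-significant Hypothesis 1 would seem to say more than it can.

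**Working it through.** **Inputs.** From Planned Analyses, Hypothesis 1: power 0.80, effect size 0.30, total N=108, chi-square test; earlier study chi-square 18.4, N=207, d=0.62. From Trial Design and Objectives: two groups and two outcome categories, so df = (2−1)(2−1) = 1. Assumed, because not stated: two-sided alpha 0.05 and equal groups (54 each). No dropout allowance is applied; the section on monthly calls counts un-contactable women as smoking.

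**Step 1. Reproduce 108.** For a chi-square test the noncentrality is λ = N·w². With w=0.30 and 80% power:
- df=1: N = (1.960+0.842)²/0.30² = 7.85/0.09 = 87.2, so 88. At N=108, λ = 108×0.09 = 9.72 and power is 87.7%.
- df=2: N=108 (power 80.4%).
- df=3: N=122. df=4: N=133.

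The planned 2×2 test therefore gives 88. The printed 108 is an exact match for df=2, which this design does not have.

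**Step 2. Put the earlier study on the same scale.**
- w = sqrt(χ²/N) = sqrt(18.4/207) = 0.298.
- d = 2w/sqrt(1−w²) = 0.596/0.954 = 0.625, which agrees with the printed 0.62.
- In reverse, w=0.30 gives d = 0.60/sqrt(0.91) = 0.63.

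So w=0.30 and d=0.62 are the same effect. In quit rates with equal groups, w=0.30 from a 9% base is 9% vs 34%, against the earlier study's 9% vs 32%. The rounded rates give a chi-square a little below 18.4 (17.4 for 34/105 vs 9/102 without continuity correction, w=0.29); this changes nothing of substance.

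**Step 3. Read 0.30 as d.**
- w = d/sqrt(d²+4) = 0.30/sqrt(4.09) = 0.148, half of 0.298.
- Required N = 7.85/0.148² ≈ 357. The two-sample normal approximation gives 350.
- Power at 108 (df=1): 33.8%; t-test 33.9%; normal approximation 34.4%. One-sided, it is 46% to 47%.

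**Step 4. What 108 can detect (df=1).** The smallest w at 80% power is 2.80/sqrt(108) = 0.27, which is d = 0.54/sqrt(1−0.073) ≈ 0.56.

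| Effect | Example quit rates | Power at 108 |
|---|---|---|
| w=0.30 (d=0.63) | 20% vs 48%, or 25% vs 54% | about 88% |
| w≈0.27 (d≈0.56) | 20% vs 45%, or 25% vs 51% | about 80% |
| w=0.148 (d=0.30) | 20% vs 33% | about 34% |

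**The case against.** Several points on the other side are sound and limit the finding.

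- **A reader might infer that the trial has 34% power.** The article does not support that. The planned test is a chi-square, 0.30 is the customary medium value of w, and d=0.30 cannot produce 108. The likelier reading is w, with about 88% power. The 34% applies only to an effect about half the earlier one.
- **A reader might infer that the trial lacks 80% power for anything smaller than the earlier contrast.** That is false: 80% is reached at w of about 0.27, against the earlier 0.298. The margin is narrow, but it exists.
- **A reader might conclude that the authors used df=2.** The match is exact but inferred. With df=1, an alpha of 0.025 gives 106, and adding about 20% for dropout to 88 gives 106 to 110. The article states neither; its multiplicity adjustment is attached to Hypothesis 2. Whatever the source, 108 exceeds 88, so the discrepancy alone does no harm.
- **A condensed article leaves detail to the full protocol.** This is fair for alpha and dropout. It does not answer the main point, because the prior effect, the argument for reducing it, the planning value and N are all printed and do not agree.
- **Recruitment has concluded, and the article does not say how a null result will be read.** Both are true. The misreading is a risk, not a stated plan, and the remedy concerns wording and interpretation only.

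**Conclusion.** The sample-size statement is wrong as written. Read as w, 0.30 is the same effect as the d=0.62 it was meant to fall below, and the planned test needs 88. Read as d, the effect is halved as the text implies, but 108 gives about 34% power and about 350 to 357 women would be needed. No reading documented in the article makes the paragraph coherent.

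At 108 the trial is well powered (about 88%) for an effect as large as the earlier one, has 80% power only slightly below it, and is poorly powered for an effect half as large. This rests on two-sided alpha 0.05, the 2×2 chi-square test and, for the d conversions and quit-rate examples, equal groups. The equivalence of w=0.298 and d=0.62 follows from the article's own chi-square and N and needs no assumption about alpha. The degrees-of-freedom mismatch is secondary and conservative.

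**What to change.** Keep N=108 and rewrite the sample-size paragraph under Hypothesis 1:

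- Name the metric (w), the degrees of freedom (1) and the alpha. Give the reason for 108 in place of 88, or say that 108 exceeds the requirement.
- Remove the implication that 0.30 is smaller than the earlier study's effect; say that the two are equal.
- State that 108 gives about 88% power for w=0.30 (about 20% vs 48% quit), 80% only down to w of about 0.27 (d about 0.56; about 20% vs 45%), and about 34% for d=0.30 (about 20% vs 33%).
- State, before results are reported, that a non-significant Hypothesis 1 does not exclude a moderate effect of partner incentives.

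The cost is a less favourable power statement for the smaller effect that the paragraph says it expects. There are no extra participants and no change to the primary test.
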